### Study design and setting

SAFE-SSPE (clinical Surveillance vs. Anticoagulation For low-risk patiEnts with isolated SubSegmental Pulmonary Embolism) is an investigator-initiated, multicentre, randomised, placebo-controlled, double-blind, parallel-group non-inferiority trial. Patients with isolated SSPE at low risk for VTE progression or recurrence and without concomitant deep vein thrombosis (DVT) are randomly assigned in a 1:1 ratio to receive clinical surveillance plus placebo or clinical surveillance plus anticoagulation with rivaroxaban (figure 1). Randomisation is blocked and stratified by study site. To ensure concealment of allocation, the allocation sequence is generated by a data manager not involved in the study, using a computer-generated randomisation schedule. All participants, care providers, investigators, study personnel, members of the outcomes adjudication committee, data management personnel and analysts are blinded to group assignment. Eligible patients are recruited in at least 27 university and medium-volume to high-volume non-university teaching hospitals in Switzerland, the Netherlands and Canada.

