PEmb-QoL dimension scores at 30 and 90 days as well as the change in scores from baseline will be presented by treatment group as means with 95% CIs. The change in dimension scores and the differences in the change between groups will be analysed using a repeated-measures, linear mixed-effects model adjusted for the respective baseline value. Functional status, which is measured on a scale from 0 (no functional limitations) to 5 (death) at 90 days, will be presented as median and IQR and compared between groups using the non-parametric Wilcoxon rank-sum test. Count data (subsequent hospitalisations, outpatient visits) will be presented by treatment group as rate with an exact 95% Poisson CI and compared using a rate ratio and exact p value. Time-to-event outcomes (initial LOS, time to return to work/usual activities) will be presented as medians and IQRs. For LOS, we will compare groups using the Wilcoxon rank-sum test. For return to work, we will display Kaplan-Meier curves and compare groups by the log-rank test. An alpha level of <0.05 will define statistical significance.

In secondary analyses, we will calculate the cumulative incidence and the difference in cumulative incidence of VTE recurrence and clinically significant bleeding, correcting for withdrawals and losses to follow-up by censoring and for death unrelated to VTE recurrence or bleeding as a competing event. All-cause mortality will be assessed likewise, however, a competing event does not apply. In a further secondary analysis, we will use model-based approaches for all outcomes. For time-to-event outcomes (VTE recurrence, clinically significant bleeding, LOS, return to work/usual activity), we will use competing risk regression according to Fine and Gray,^70^ accounting for non-VTE/non-bleeding-related death or all-cause death as a competing event. For mortality, we will use Cox regression. For count data, we will use a negative binomial model, and also consider zero-inflation. In case of heterogeneity across sites, we will adjust models for site using random-effects models.

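### Randomisation is stratified by site, but site enters the models only if heterogeneity is seen and is not in the stated PEmb-QoL model: a minor, easily fixed data-driven choice

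*Protocol article*

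**What the plan says.** In the protocol article, the section on study design and setting states: "Randomisation is blocked and stratified by study site". No other stratification factor is named. Patients are "recruited in at least 27 university and medium-volume to high-volume non-university teaching hospitals" in three countries.

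The section on planned statistical analyses sets out the main ancillary comparisons in one paragraph:

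- PEmb-QoL scores: a "repeated-measures, linear mixed-effects model adjusted for the respective baseline value".
- Functional status: "compared between groups using the non-parametric Wilcoxon rank-sum test". Initial length of stay uses the same test.
- Counts of hospitalisations and visits: "compared using a rate ratio and exact p value".
- Return to work: "we will display Kaplan-Meier curves and compare groups by the log-rank test".

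None of these carries a site term. The next paragraph covers secondary analyses and says: "In a further secondary analysis, we will use model-based approaches for all outcomes". It lists Fine-Gray, Cox and negative binomial models and closes with the only sentence in the section that brings in site: "In case of heterogeneity across sites, we will adjust models for site using random-effects models".

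**The concern.** Stratifying the randomisation by site removes most of the chance imbalance between arms within sites. A linear model that leaves site out still counts between-site variation as noise, so its SE is too large and its test conservative whenever site relates to the outcome. Making inclusion depend on observed heterogeneity adds a model choice made from the data, for a factor that was known before the first patient was randomised.

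The objectives state a directional hypothesis for quality of life, function and resource use, and these outcomes are tested at 0.05. What is at stake is some precision, and the freedom to report one of two models for these outcomes. The text does not make clear whether the conditional sentence reaches back to the PEmb-QoL model in the paragraph before it, so both readings are worked through below.

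**Working it through.** **Inputs from the article.** 276 patients (138 per group), 5% attrition, 1.0% VTE recurrence in both groups, margin 3.5%, one-sided 5% level, at least 27 sites, stratification by site.

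**Assumptions not in the article.** Site ICC from 0 to 0.20; blocks of 4; heterogeneity judged by a likelihood-ratio test of the site variance at 5%; a normally distributed outcome at a single time point with no baseline covariate.

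**Step 1: the plan's own figure.** 138 × 0.95 = 131 evaluable per group. Exact enumeration of two binomials at 1.0%, with the one-sided 95% Agresti-Caffo upper limit compared with 3.5%, gives power 80.8%. Since 131/0.95 = 138, the total of 276 is reproduced. This point does not dispute it. It gives the size used below: 2 × 131 = 262 completers, and 276/27 ≈ 10 patients per site.

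**Step 2: site never in the model.** With allocation balanced within site, the treatment difference varies only with the within-site variance, a share (1 − ICC) of the total, while the unadjusted model uses the total. So

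- SE ratio = 1/√(1 − ICC)
- true two-sided level = 2[1 − Φ(1.96/√(1 − ICC))]

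| ICC | SE ratio | Level, formula | Level, simulated |
|---|---|---|---|
| 0.01 | 1.005 | 4.9% | 4.6–4.8% |
| 0.05 | 1.026 | 4.4% | 4.2–4.7% |
| 0.10 | 1.054 | 3.9% | 3.8–3.9% |
| 0.20 | 1.118 | 2.8% | 2.9–3.0% |

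The simulation used 262 patients in 27 sites, of even and of skewed size, with 6,000 replicates under the null. Its ratio of model SE to empirical SE is slightly below the formula: 1.02, 1.05 and 1.10–1.11 at ICC 0.05, 0.10 and 0.20.

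**Step 3: site added only when heterogeneity is significant at 5%.** Mean SEs are for even site sizes.

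| ICC | Trials in which the rule triggers | Mean SE, always adjusted | Mean SE, conditional | Conditional ÷ always |
|---|---|---|---|---|
| 0 | about 4% | 0.1228 | 0.1232 | 1.003 |
| 0.01 | 8–10% | 0.1225 | 0.1231 | 1.005 |
| 0.05 | 41–48% | 0.1204 | 0.1212 | 1.007 |
| 0.10 | 80–81% | 0.1175 | 0.1179 | 1.003 |
| 0.20 | 98–99% | 0.1109 | 0.1109 | 1.000 |

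Under the null, the rule's type I error is 4.5–5.2% and its model SE divided by empirical SE is 0.99–1.01.

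**Step 4: power** for an assumed effect of 0.346 SD, even site sizes (3,000 replicates).

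| ICC | No site term | Conditional | Always |
|---|---|---|---|
| 0.05 | 79.9% | 80.6% | 81.2% |
| 0.10 | 80.4% | 82.8% | 82.9% |
| 0.20 | 82.0% | 87.2% | 87.2% |

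**Step 5: would stratified rank tests help?** A simulation of the site-stratified van Elteren test against the plain Wilcoxon test (262 patients, 27 sites) shows a loss of about 2–5 power points at ICC 0. At ICC 0.10 the result lies between about 1 point lost and 2 gained. Only at ICC 0.20 is there a gain, of about 2–5 points.

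**The case against.** The strongest reply is that this is a preference about efficiency. A conservative test does not inflate false positives, only ancillary outcomes and secondary models are involved, and the conditional rule largely corrects itself: when site matters it usually triggers, and when it does not trigger little is lost. Step 3 bears this out under a 5% trigger, so this part of the reply stands. It does not explain why a factor fixed by the design should be optional.

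A reader might infer several stronger things that the article does not support.

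- *That the ancillary comparisons in general use a model picked from the data, with intervals that are too wide.* The Wilcoxon, log-rank and exact rate tests are fixed in advance and do not depend on heterogeneity. The 5–12% SE excess at ICC 0.10–0.20 belongs to never adjusting, not to the conditional rule.
- *That sites of about 10 patients leave too little power to detect heterogeneity.* That is fair at ICC 0.05 or below. At 0.10 and 0.20, where omission would cost something, detection is about 80% and 98–99%.
- *That every test should be stratified by site.* Step 5 shows that for rank tests this can lose power.
- *That intervals are too wide in the Cox and Fine-Gray models.* There, leaving out a covariate mainly pulls the estimate towards the null.
- *That the unstated heterogeneity criterion is itself a defect.* The analysis plan may define it. The conditional rule is stated in the article and can be judged as it stands.

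The linear figures also ignore the baseline score, which may absorb part of the site variation, so the residual ICC in the PEmb-QoL model could be lower than assumed.

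**Conclusion.** The point holds as a minor one. The article stratifies by site, leaves site out of the stated PEmb-QoL model, and lets it into models only on evidence of heterogeneity.

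If the conditional sentence does not reach the PEmb-QoL model, the SE is too large by about 3%, 5% or 12% at ICC 0.05, 0.10 or 0.20, with the conservative levels shown in Step 2. If it does reach that model, and the trigger is a 5% test, the loss is under about 1% of the SE and type I error stays near nominal; the weakness is then mainly the avoidable choice after seeing the data. A much stricter trigger would move the result towards the first set of figures.

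The ICC values are assumptions, since the article gives none, and the figures are for a linear outcome, so they do not measure the loss in the count models. The primary Agresti-Caffo analysis contains no model and is unaffected.

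**What to change.** Delete the condition. State that a site random intercept is included in all cases in the PEmb-QoL mixed model and in the secondary count models, and set before unblinding a rule for pooling very small sites within country.

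Leave the primary analysis and the Wilcoxon, log-rank and exact rate tests as stated. For the secondary Cox and Fine-Gray models, also make one fixed choice in advance; about 262 × 1.0% ≈ 3 recurrences are expected, too few to estimate site effects usefully for that outcome.

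The cost is a change of wording. Site is already recorded because the randomisation uses it, and the only added work is the pooling rule.

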### Data monitoring and interim safety analysis

An independent Data and Safety Monitoring Board (DSMB) consisting of three members unaffiliated with any of the participating institutions will evaluate unblinded interim safety results after 100 and 190 randomised patients have completed the 90-day follow-up. To monitor recurrent VTE in the intervention group, formal interim analyses will be performed using a Bayesian approach. Based on literature,^23^ we expect a frequency of VTE recurrence of 1.0% (0%–4.5%). We regard a frequency of >5% in the surveillance group as clinically unacceptable. We will calculate the prior probability distribution of events based on the expected frequency as well as the posterior probability distribution using actually observed data at each interim analysis. Based on the posterior distribution, we will calculate the probability that the true proportion of VTE recurrence in the surveillance group exceeds the threshold of unacceptable frequency. If the probability of exceedance is >70%, the surveillance arm will be considered inferior and the DSMB will recommend to stop the trial. The final decision will lie with the Steering Committee. This procedure is conservative regarding the type I error rate; therefore, we will not adjust the significance level in the final analysis.

### Patient and public involvement

We have partnered with a group of patients who had recently experienced PE in the planning process of this trial, including the selection of patient-centred outcomes, the establishment of a safe surveillance schedule and the determination of a clinically acceptable non-inferiority margin. Patients are not involved in the recruitment and conduct of the study or the dissemination of study results.

### Data sharing

After publication of the study results, a de-identified patient-level data set relating to the primary publication along with the latest version of the study protocol, the informed consent form, the statistical analysis plan, the analysis code and the data management plan of the study will be made publicly available in the *Bern Open Repository and Information System* (*BORIS) Research Data*.

## Ethics and dissemination

This trial is conducted in accordance with the Declaration of Helsinki, the International Council on Harmonization Good Clinical Practice guidelines, and all applicable national legal and regulatory requirements. Authorisation by the local Ethics Committees and Swissmedic has been obtained in Switzerland, and the submission process to the relevant Dutch and Canadian Ethics Committees and regulatory authorities is ongoing. All changes in research activity or unanticipated problems involving risks to human subjects will be reported promptly to the ethics committees. All participating investigators/institutions will permit study-related monitoring, audits, ethics committee reviews and regulatory inspections, and will provide direct access to source documents and data. Protection of confidentiality is ensured according to regulatory requirements.

Study personnel informs eligible patients with a diagnosis of isolated SSPE about all aspects of the study participation, including the goals, procedures and potential risks/benefits associated with the study. Potential participants are informed that the decision to participate in the study is entirely voluntary and that they may withdraw from the study at any time, with no effect on their current or future treatment. Written informed consent is obtained from all eligible patients prior to any study-related procedure, including bilateral whole-leg CUS. The primary study results will be presented at scientific conferences and published in a peer-reviewed medical journal. We also plan local presentations for physicians at the participating sites. Participants will receive a letter with the study results explained in lay language. Further public dissemination of the results is planned through publications in the lay press and via social media.

## Conclusion

The SAFE-SSPE trial addresses an important gap of knowledge, the optimal management of SSPE, and represents the first randomised, direct comparison of clinical surveillance alone versus anticoagulant treatment for low-risk patients with isolated SSPE. As the number of SSPE patients who may eventually receive anticoagulant treatment is likely to rise in the future with the further dissemination and advancement of CTPA technology, a strong scientific basis for withholding anticoagulation in low risk patients with SSPE is urgently needed. The results of this trial have the potential to improve quality and efficiency of care by reducing bleeding episodes and resource utilisation and increasing health-related quality of life.

### Current status of the SAFE-SSPE trial

Patient recruitment has started in May 2020; by July 2020, six patients have been enrolled in the trial. Follow-up of the last participant is expected to be completed in February 2024.
